## Methods

### Objectives

### Study Design

This study adopts a crossover randomized controlled trial (RCT) to examine how ETU influences objective and subjective sleep in older adults aged 60 to 75 years. Three conditions will be compared: (1) passive ETU, (2) active ETU, and (3) nondigital activity.

After completing an initial baseline assessment via survey, participants will undertake a 5-week schedule composed of 3 separate, one-week intervention periods. At baseline, each participant is randomized to one of six possible sequences of the 3 conditions (passive ETU, active ETU, nondigital; 3!=6). Participants then complete 3 one-week intervention periods in their assigned order, separated by 2 one-week washouts (total duration: 5 wk). We chose a 7-day washout period because systematic reviews of digital detox interventions often recommend this duration for detoxification [19].

During each intervention week, participants will maintain a daily evening log to record subjective sleep quality, ETU, and the comfort of using a wearable headband. Objective sleep outcomes will be assessed using electroencephalography (EEG) collected via a headband (Muse-S Athena, InteraXon, Toronto, ON, Canada), while self-reported logs capture subjective experiences. This crossover design allows for within-subject comparisons, thereby reducing variability, controlling for individual differences in sleep patterns, and confounding factors, while enhancing statistical power.

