#### Primary Outcome Measures

##### Overview

The primary outcomes of this study focus on changes in objective sleep onset latency (SOL) and wake after sleep onset (WASO) assessed using objective data collected via the MUSE EEG headband. This wearable device records brainwave activity throughout the night, enabling detailed analysis of various sleep parameters. The primary sleep parameters are provided below.

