##### Wake After Sleep Onset (WASO)

WASO measures the cumulative amount of time (in minutes) a participant spends awake after initially falling asleep until final morning awakening. Elevated WASO values may indicate fragmented or disrupted sleep, which can negatively affect sleep quality and daytime functioning. It is automatically computed by summing detected wake periods within the sleep period time by the MUSE device algorithm.

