#### Subjective Sleep Quality

Each morning, participants will complete a low-burden Single-Item Sleep Quality Scale, a validated tool designed to assess overall perceived sleep quality [24]. We chose this brief item to minimize burden and support daily completion in older adults. This brief measure captures participants’ evaluations of how well they slept the previous night, ranging from 0 (terrible) to 10 (excellent). Subjective ratings are analyzed alongside objective EEG outcomes as complementary indices of sleep and are tested across passive ETU, active ETU, and nondigital activity.

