The coprimary outcomes are SOL and WASO derived from the MUSE EEG. The primary objective compares combined ETU versus nondigital activity, where ETU is defined by collapsing the 2 technology conditions (passive and active) into a single ETU category. This will be tested as a prespecified linear contrast of the condition marginal means from a linear mixed-effects model (LMM). For each primary outcome (SOL and WASO), we will fit an LMM with fixed effects for condition and period and a participant-specific random intercept. The LMM analyses will use all available valid nights. In addition to the prespecified combined-ETU contrast, we will estimate all pairwise condition contrasts (active vs passive, active vs nondigital, passive vs nondigital) using the Tukey adjustment. Model-based estimates, 95% CIs, and *P* values will be reported, together with a standardized within-participant effect size. Multiplicity control across the 2 coprimary endpoints (SOL and WASO) will be performed using the Holm procedure with a family-wise α of .05 (2-sided). If at least one coprimary endpoint is statistically significant after the Holm adjustment, we will proceed to confirmatory testing of the prespecified key secondary outcomes; otherwise, these secondary outcomes will be reported as exploratory. Model assumptions will be checked; if needed, outcomes will be transformed or analyzed using an appropriate generalized mixed model.

Key secondary objective outcomes are TST, SE, and sleep stages (REM%, Deep% [SWS], Light%). These outcomes will be analyzed using the same LMM framework (fixed effects for condition and period; random participant intercept), with Tukey adjustment for pairwise condition comparisons. To control for multiplicity across the key secondary outcomes, *P* values will be adjusted using Holm’s procedure (2-sided α=.05), applied only if the gatekeeping criterion on the coprimary outcomes is met. All remaining outcomes (eg, subjective sleep, adherence, and comfort) will be treated as exploratory and interpreted primarily via effect estimates and 95% CIs.

We will briefly explore how subjective sleep aligns with objective measures using simple descriptive statistics (mean, SD and median, IQR). The full analysis code will be included as a supplementary file (including SPSS syntax and output) when the main study is reported. The statistical plan for each research question is presented in Table 1.

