## Discussion

### Principal Findings

This study aims to evaluate how ETU and types of evening activities, specifically Active technology use, Passive technology use, and nondigital activity, affect both objective sleep parameters and subjective sleep quality in older adults. In this 3-period crossover study of older adults, we hypothesize that, compared with a nondigital presleep activity, both passive and active ETU will be associated with longer SOL and greater WASO on EEG. We further expect active technology use to show the largest effects. As a secondary expectation, subjective sleep quality ratings will be lower on technology-use nights and will broadly follow the objective patterns.

A previous study revealed in OA that screen use before bed is positively associated with subjective sleep health [15], contrary to the conventional opinion that screen use has a negative relationship in the younger population [30-32]. This variability is an empirical motivation to test whether effects differ by activity type. Our within-person crossover study compares active and passive ETU to a nondigital activity, allowing us to determine if any effects are specific to the activity without inferring mechanisms. Evening activities can affect presleep arousal through 2 main routes: light exposure from screens (blue-enriched light) [3,33] and cognitive/emotional engagement [5]. The study expects that active ETU (interactive gaming) will produce the highest engagement/arousal and screen exposure; passive ETU (neutral, low-arousal videos) will produce moderate-light engagement; and nondigital reading will be lowest on both. Accordingly, we hypothesize that active ETU has a greater impact on disrupting objective sleep and lower subjective sleep quality compared with passive ETU and nondigital technology nights.

Older adults are an important population for studying the underlying mechanisms related to sleep. Age-related changes in circadian and homeostatic regulation often lead to earlier sleep onset, reduced amplitude, and more fragmented sleep [34]. Consequently, factors like presleep arousal through the use of technology become especially significant. Additionally, changes in ocular and retinal function can affect spectral sensitivity, meaning the way older adults perceive light may differ from that of younger individuals [35].

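### The exploratory look at how subjective sleep aligns with EEG sleep uses only one-variable summaries, so it cannot show association at the level of nights or persons, although paired nightly data are collected

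*Protocol article*

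**What the plan says.** The Statistical Analysis Plan section of the protocol article fixes the method for relating the two kinds of measure: "We will briefly explore how subjective sleep aligns with objective measures using simple descriptive statistics (mean, SD and median, IQR"). No paired statistic is named there or elsewhere in the article.

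The section on subjective sleep quality gives the ratings this role: "Subjective ratings are analyzed alongside objective EEG outcomes as complementary indices of sleep". Table 1 analyses the rating as an outcome, with a linear mixed model (LMM) on condition and period and Tukey-adjusted contrasts. It does not relate the rating to any EEG measure. The Principal Findings section adds the expectation that the ratings "will broadly follow the objective patterns".

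Both halves of each pair are collected nightly:

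- Rating: "Each morning, participants will complete a low-burden Single-Item Sleep Quality Scale", "ranging from 0 (terrible) to 10 (excellent").
- EEG: "This wearable device records brainwave activity throughout the night, enabling detailed analysis of various sleep parameters".
- Duration: "Participants then complete 3 one-week intervention periods in their assigned order".

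**The concern.** To say that two measures align is to say something about how they vary together. A mean, SD, median or IQR is computed on one variable with no reference to the other. If the report carries out the sentence as written, it will list summaries of the 0-10 rating beside summaries of sleep onset latency (SOL), wake after sleep onset (WASO) and the rest. It will then have no basis for saying that a poor EEG night is felt as a poor night, or that people with poor EEG sleep rate their sleep lower.

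What is at stake is small but specific. The trial presents the combination of EEG and self-report as a strength. Without a named paired measure, the report must either stay silent on night- and person-level association or choose a measure after the data have been seen.

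**Working it through.** The plan gives no figure for this analysis, so there is none to reproduce. The check has three parts.

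**1. Do the named statistics depend on the pairing?**

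This was checked with illustrative data (assumed, not from the trial): 1155 SOL values from a log-normal distribution (log-mean 3, log-SD 0.6) and 1155 ratings from a normal distribution (mean 6.5, SD 1.8), rounded and limited to 0-10. The same two sets of values were paired in three ways.

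| Pairing | SOL mean / SD / median / IQR | Rating mean / SD / median / IQR | Spearman correlation |
|---|---|---|---|
| Same order | 23.2 / 15.4 / 19.7 / 13.2-29.3 | 6.55 / 1.84 / 7 / 5-8 | 0.99 |
| Shuffled | identical | identical | -0.03 |
| Reverse order | identical | identical | -0.99 |

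The result does not depend on the distributions chosen: re-ordering one variable never changes its own summaries. The same holds within a condition. Re-pairing nights inside one participant's week leaves that week's summaries unchanged for both measures, so tabulating by condition does not recover night-level association.

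**2. How many pairs are there?**

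- Participants: 55 (target in Population and Recruitment; the abstract says approximately 55).
- Nights: 3 weeks x 7 = 21 per participant.
- Maximum pairs: 55 x 21 = 1155 nights, or 55 x 3 = 165 week means.

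**3. How precise would a paired estimate be?**

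For a within-person correlation near zero, SE(r) is about 1/sqrt(N - k - 1), where N is the number of pairs and k the number of means removed. With k = 55, only participant means are removed. With k = 165, all participant-by-week means are removed, which allows for nights clustering within weeks. The article does not give the share of valid nights, so a range is shown, with no dropout assumed.

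| Valid nights per week (assumed) | N | SE, k = 55 | SE, k = 165 |
|---|---|---|---|
| 7 of 7 | 1155 | 1/sqrt(1099) = .030 | 1/sqrt(989) = .032 |
| 6 of 7 | 55 x 18 = 990 | 1/sqrt(934) = .033 | 1/sqrt(824) = .035 |
| 4 of 7 | 55 x 12 = 660 | 1/sqrt(604) = .041 | 1/sqrt(494) = .045 |

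With week means only, SE is about 1/sqrt(165 - 55 - 1) = 1/sqrt(109) = .096.

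The person-level association rests on 55 persons and is less precise. The Fisher-z 95% CI is tanh(atanh(r) ± 1.96/sqrt(52)), which gives -0.17 to 0.36 for r = 0.1, 0.04 to 0.52 for r = 0.3, and 0.27 to 0.68 for r = 0.5.

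**The case against.** **The condition-level question is already covered.** This stands. A reader might infer that the plan cannot test the expectation in Principal Findings. The article does not support that. Read in context, the patterns referred to are the condition effects set out just before. Table 1 provides an LMM of the rating, with contrasts and intervals, and the same model structure for the objective outcomes. Setting the two sets of contrasts side by side checks the expectation.

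**Condition comparisons do not mix between-person and within-person differences.** This also stands. A reader might suspect such mixing, but every participant is planned to receive all three conditions and the models carry a participant intercept. Those contrasts are therefore mainly within-person, apart from what incomplete data introduce.

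**The article does not promise agreement.** Correct. Its verb is *aligns*, and agreement in the sense of limits of agreement would not apply, because one measure is a unitless rating and the other is not (for example, "WASO measures the cumulative amount of time (in minutes) a participant spends awake"). The missing item is a measure of association.

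**The layout is not stated.** The article does not exclude tabulating SOL or WASO by rating level, and such a table would change with the pairing. This stands in part. But nothing in the text indicates that layout, it would pool nights across persons, and it would give no estimate with an interval.

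**The analysis is brief and exploratory, and a condensed article leaves details to a fuller plan.** The first half limits the severity. The second does not remove the point, because the article does not leave the method open: it names one, and the one named does not fit the question.

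**Conclusion.** The point holds as a minor one. The method fixed for exploring alignment consists of univariate statistics, which carry no information on whether nights or persons with worse EEG sleep are rated worse. That much is a mathematical property and needs no assumption beyond reading the sentence as written.

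The feasibility figures do rest on assumptions: 55 completers, 6 of 7 valid nights, a rating for each of those nights, and independent nights once the participant or participant-week means are removed. On these, a within-person correlation could be estimated with an SE of about .03 to .04, roughly a third of the .10 available from week means. Fewer valid nights or dropout would widen this, as the range above shows.

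The coprimary tests of SOL and WASO, the key secondary outcomes and the multiplicity scheme do not depend on this sentence.

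**What to change.** Replace the sentence with an exploratory paired analysis, restricted to valid nights that have a morning rating. Either of these would serve:

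- a repeated-measures correlation of the rating with each EEG measure; or
- an LMM of the nightly 0-10 rating on person-mean-centred SOL, WASO and total sleep time, plus the person means of each, with random intercepts for participant and participant-by-period. The centred terms give the night-level association and the person means the person-level one.

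Report the estimate and 95% CI, labelled exploratory. Leave the condition-level comparison to the Table 1 models.

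State that this analysis uses nightly values. The Statistical Analysis Plan section says that all analyses use participant-level week means, and later that the LMMs use all available valid nights, so the exception should be explicit. Settle the choice before the condition labels are unmasked.

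The cost is a few lines of syntax on data already collected and a little more exploratory output to report. No new measurement is needed.

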### Ethical Considerations

The study will adhere to ethical standards as outlined by the Swedish research ethics framework. Ethical approval was obtained from the Regional Ethical Review Board prior to study initiation (Dnr 2025-02006-01). All participants will receive comprehensive information about the study’s aims, procedures, potential risks, and their rights before providing written informed consent.

Participant confidentiality will be maintained through strict data management procedures. All data will be stored securely, ensuring that individual identities cannot be traced. All study data are stored on an encrypted, firewall-protected BTH server. Records are pseudonymized; identifiers are not stored with research data. Participation in the study is entirely voluntary, and participants may withdraw at any time without consequence. Procedures comply with GDPR, including participants’ rights to access, rectification, and deletion.

## Results

Participant recruitment and data collection commenced in the Fall of 2025. Recruitment is ongoing and will continue through Summer 2026 or until the target sample size is reached. The completion of data collection is projected for Spring 2027. We hypothesize that older adults exposed to ETU before bedtime will show significant differences in primary objective sleep outcomes compared with those exposed to nondigital activity. We also hypothesize that Passive and Active technology use will show significant differences in sleep outcomes among themselves and versus nondigital activity.

In the final trial report, the following data will be presented.

Number of participants screened, enrolled, randomized, and completed each intervention phaseReasons for dropouts, exclusions, and nonadherence during any of the 3 conditionsBaseline characteristics of all the variables measuredResults of the statistical analysis based on the research questions of the primary and secondary outcome measures

## Discussion

### Principal Findings

This study aims to evaluate how ETU and types of evening activities, specifically Active technology use, Passive technology use, and nondigital activity, affect both objective sleep parameters and subjective sleep quality in older adults. In this 3-period crossover study of older adults, we hypothesize that, compared with a nondigital presleep activity, both passive and active ETU will be associated with longer SOL and greater WASO on EEG. We further expect active technology use to show the largest effects. As a secondary expectation, subjective sleep quality ratings will be lower on technology-use nights and will broadly follow the objective patterns.

A previous study revealed in OA that screen use before bed is positively associated with subjective sleep health [15], contrary to the conventional opinion that screen use has a negative relationship in the younger population [30-32]. This variability is an empirical motivation to test whether effects differ by activity type. Our within-person crossover study compares active and passive ETU to a nondigital activity, allowing us to determine if any effects are specific to the activity without inferring mechanisms. Evening activities can affect presleep arousal through 2 main routes: light exposure from screens (blue-enriched light) [3,33] and cognitive/emotional engagement [5]. The study expects that active ETU (interactive gaming) will produce the highest engagement/arousal and screen exposure; passive ETU (neutral, low-arousal videos) will produce moderate-light engagement; and nondigital reading will be lowest on both. Accordingly, we hypothesize that active ETU has a greater impact on disrupting objective sleep and lower subjective sleep quality compared with passive ETU and nondigital technology nights.

Older adults are an important population for studying the underlying mechanisms related to sleep. Age-related changes in circadian and homeostatic regulation often lead to earlier sleep onset, reduced amplitude, and more fragmented sleep [34]. Consequently, factors like presleep arousal through the use of technology become especially significant. Additionally, changes in ocular and retinal function can affect spectral sensitivity, meaning the way older adults perceive light may differ from that of younger individuals [35].

Digital usage patterns among older adults also vary, typically involving more passive activities, such as viewing content, communicating, and playing simple games. These behaviors influence cognitive and emotional engagement [36]. Therefore, it is important, both demographically and conceptually, to investigate how different types of evening activities, such as those involving screen light and engaging content, affect sleep quality in older adults.

Unlike much of the existing research, which focuses primarily on children and adolescents [32,37], this study examines an underexplored demographic: older adults who are increasingly active users of digital technology and often have health issues linked to poor sleep.

### Methodological Consideration

This study will use a randomized crossover design. This within-subject approach limits confounding, minimizes the influence of inter-individual variability, and increases statistical power, which is especially important given the moderate sample size [3,4]. Objective sleep measures will be captured via a wearable EEG headband (MUSE), allowing for naturalistic, at-home sleep tracking that is both minimally intrusive and ecologically valid as it supports generalizability to real-world settings [29]. Additionally, participants will complete daily self-report ratings assessing their subjective sleep quality and mood. Single-item sleep quality measures have limitations because they lack the detail needed to capture the multi-dimensional nature of sleep problems, leading to issues with sensitivity, content validity, and reliability. However, the item is low-burden and has good construct validity [24]. The inclusion of a brief affective experience scale, adapted from validated instruments such as the Visual Analog Mood Scales [25], Positive and Negative Affect Schedule [26], and the User Engagement Scale [27], enables examination of psychological and experiential factors that may mediate the relationship between ETU type and sleep outcomes. Combining objective EEG data with subjective daily logs will provide a holistic, multidimensional understanding of sleep quality [18].

In this randomized crossover trial, participants will receive structured instructions and technical support to guide them in using the EEG headband and completing the assigned activities. These elements are designed to support compliance, usability, and data completeness. In this study design, there is a bias due to the carryover effect (residual effects of one condition influencing the next) and period/sequence effects (time- or order-related differences) [38]. These biases will be mitigated with a one-week washout period and by randomizing condition order, analyzing participant-level week means (which dampens night-to-night variability). This will also help to reduce weekend bias, as weekend sleep might differ from weekday sleep.

It is important to consider certain limitations of the study design and the expected results. Randomized crossover trials might increase the risk of participant dropout because, for a participant’s data to be included in the analysis, they must complete all intervention periods. To reduce attrition and support adherence, participants receive direct contact details (phone and email) for the lead author ([name]) and the university research clinic. They are also welcome to visit the clinic if they wish to discuss any issues. Recruitment and the initial information meeting are scheduled flexibly with 4 alternative time slots. Adherence is monitored via the daily log. If participants drop out before finishing all interventions, their data may be unusable, reducing the effective sample size and potentially introducing bias [39]. Although the crossover design helps control for inter-individual differences, subjective perceptions of each intervention may still influence self-reported sleep outcomes (eg, enjoyment or bias toward novelty). Nonadherence and usability challenges with the EEG device may affect the implementation of the intervention. Some participants may not follow the assigned activity consistently or may experience discomfort while using the MUSE EEG headband, which can impact their sleep. Technical issues or limited digital literacy could further reduce compliance or introduce usage bias [40]. Therefore, we will report the number of valid nights per condition and provide an attrition/participant flow summary in our results manuscript, allowing readers to assess compliance. These risks will be mitigated through initial training, daily logs, and reminders, but complete control is not guaranteed. Regarding the results, the findings will reflect the experiences of relatively healthy, digitally literate older adults and may not generalize to older populations with cognitive impairments or severe sleep disorders. Furthermore, the use of EEG headbands at home relies on participant compliance and technical reliability, which may affect data completeness.

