### Statistical Analysis Plan

Analyses will be conducted in SPSS Statistics (version 29.0.x; IBM Corp, Armonk, NY); the exact patch (eg, 29.0.2) will be reported at analysis. Descriptive statistics will be used to summarize demographic information, baseline sleep characteristics, chronotype prevalence, overall intervention adherence (percentage of nights completed; minutes engaged), perception ratings (calmness, stress, engagement, enjoyment, meaningfulness on 0‐10), and EEG headband comfort (1‐5 Likert), presented as mean (SD) or median (IQR), as appropriate.

Primary and secondary sleep outcomes will be derived from MUSE EEG auto-scoring using the device’s standard algorithm. This study does not include manual rescoring or a new polysomnography comparison; instead, we rely on published validation studies demonstrating agreement with polysomnography/manual scoring [28,29]. All analyses will use participant-level week means (nightly values averaged within each intervention week/condition). Before analysis, we will check data quality. A night is classified as VALID if the device records ≥4 hours within the main sleep window and yields plausible values (eg, TST 2‐12 h, SOL 0‐180 min, WASO 0‐240 min); otherwise, it is INVALID. All the valid nights will be included in the analysis. During the analysis, the data analyst will be blinded to intervention allocation. Unblinding will occur only after the analysis code is finalized, outputs are generated, and the primary results are locked. Participant-level week means (nightly values averaged within each intervention week/condition) will be calculated for descriptive purposes.

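### Week means over valid nights do not fix the weekend share, and the coprimary model has no weekend term, so condition-dependent loss of weekend nights can bias the ETU-versus-nondigital contrast

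*Protocol article*

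**What the plan says.** The Methodological Consideration section of the protocol article lists design features meant to limit bias: the washout, the randomized order and "analyzing participant-level week means (which dampens night-to-night variability". It then adds: "This will also help to reduce weekend bias, as weekend sleep might differ from weekday sleep". Of these features, week averaging is the one that bears on days of the week.

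The Statistical Analysis Plan section sets the data rules. On validity: "A night is classified as VALID if the device records ≥4 hours within the main sleep window and yields plausible values". On retention: "All the valid nights will be included in the analysis". Neither rule mentions the day of the week.

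The same section describes the unit of analysis in three ways. First: "All analyses will use participant-level week means (nightly values averaged within each intervention week/condition". Later, week means "will be calculated for descriptive purposes". Then, for the coprimary outcomes: "The LMM analyses will use all available valid nights".

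For SOL and WASO the model is fixed: "we will fit an LMM with fixed effects for condition and period and a participant-specific random intercept". Table 1 repeats it for the key secondary EEG outcomes. The primary test is the combined ETU (active and passive) versus nondigital contrast.

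**The concern.** Each condition lasts one week, so a complete period contains two weekend nights in seven whatever day it starts on. The weekend difference then adds the same amount to every condition mean and cancels. Once nights drop out as invalid, the share is no longer fixed at 2/7, and nothing in the data rules or the model restores it. If the night-level description governs, the averaging that the article relies on is not part of the coprimary analysis at all.

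At stake is the primary contrast. If weekend nights are lost more often under one condition than another, part of the weekend-weekday difference is read as an effect of evening technology. The limitations text promises the number of valid nights per condition, but a total does not reveal a shift in the weekday/weekend mix.

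**Working it through.** **The plan's own figures.** The article gives no weekend difference, no rate of invalid nights and no SD. The inputs behind the target of 55 are in an appendix that is not shown, so there is no stated figure to reproduce on this point.

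**Formula.** With d the weekend-minus-weekday difference in minutes and a true condition effect of zero:

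bias = d × (mean weekend share in the two ETU conditions − weekend share in nondigital).

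The formula needs no SD.

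**Inputs.** From the article: seven nights per condition, hence five weekday and two weekend nights. Assumed: d = 15 min (range 10 to 25); weekday validity 0.90 in all conditions; weekend validity 0.90 in the nondigital week and lower in ETU weeks.

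**Complete weeks.** The share is 2/7 = 0.286 in every condition, so the bias is 0. Equal loss in all conditions also gives 0.

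**Scenario A: weekend validity 0.90 nondigital, 0.75 passive, 0.50 active.** Expected valid weekday nights: 5 × 0.90 = 4.5.
- Nondigital share: 1.8 / 6.3 = 0.286
- Passive share: 1.5 / 6.0 = 0.250
- Active share: 1.0 / 5.5 = 0.182
- ETU mean: (0.250 + 0.182) / 2 = 0.216
- Gap: 0.216 − 0.286 = −0.070
- Bias at 15 min: −1.05 min (−0.7 at 10 min, −1.7 at 25 min)

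**Scenario B: weekend validity 0.50 in both ETU conditions.**
- Gap: 0.182 − 0.286 = −0.104
- Bias at 15 min: −1.56 min (−1.0 at 10 min, −2.6 at 25 min)

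A simulation of both scenarios at 15 min (55 participants, night SD 20 min, 500 replicates) gave −0.98 and −1.67 min without a weekend term, and +0.10 and −0.08 with one. The sign reverses if the nondigital week loses more weekend nights, or if the weekend difference is negative.

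**Does the unit of analysis matter?** A second simulation (400 replicates per setting, 55 participants, six sequences, participant SD 15 min, night SD 20 min) reversed the loss: half of nondigital weekend nights lost, against 10% in ETU weeks, with 10% of weekday nights lost throughout. The formula gives +0.104 × d.

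| d | Formula | Night-level model | Week-mean model | Night-level + weekend term |
|---|---|---|---|---|
| 10 min | 1.04 | 1.12 to 1.19 | 1.21 to 1.28 | 0.03 to 0.09 |
| 20 min | 2.08 | 2.05 to 2.16 | 2.22 to 2.32 | −0.10 to 0.01 |

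Ranges cover a participant-by-week SD of 0 and 8 min. The bias appears under either unit, and the term removes it in the night-level model.

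With no participant-by-week variation, the false-positive rate of a single unadjusted .05 test was 0.11 (night-level) and 0.15 (week-mean) at d = 10, and 0.28 and 0.38 at d = 20. These rates depend on the assumed SDs and do not include the planned Holm step.

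**The case against.** The strongest reply is that the sentence is hedged and, for complete weeks, correct: averaging is said to help, not to remove the bias. That stands, and the point is not that the article makes a false statement.

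It can also be said that the documents supply neither ingredient. Weekend sleep is said only to be possibly different. Validity depends on recording length and plausible values, not on completing the activity, so a skipped session does not invalidate a night. The headband is worn the same way in all conditions. Table 1 does hypothesize more dropout and nonadherence under active ETU, which makes equal participation unsafe to assume, but this is not evidence that weekend recordings fail more often there. This objection stands too, and it makes the bias conditional.

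A day-of-week covariate might be thought a detail for a fuller analysis plan. But the article states its own remedy and its own model, and the remedy does not do the job for incomplete weeks.

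A reader might go further and infer that omitting the weekend term makes the reported standard error too large. That does not hold in general. In a week-mean model with equal shares the weekend difference cancels; the simulated ratio of reported to true standard error was 0.91 to 1.04, with no systematic excess (Monte Carlo error about 3.5%). In a night-level model without within-week correlation the ratio was about 1.02 to 1.09 with a weekend difference of 10 or 20 min, and the excess was present even with no nights lost. With a participant-by-week SD of 8 min it was 0.71 to 0.82, so the standard error was too small. The article says nothing that fixes the direction.

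**Conclusion.** The point holds as a conditional weakness in the stated analysis. Averaging valid nights does not guarantee a common weekend share, the coprimary model does not adjust for it, and the text is inconsistent on whether averaging enters that model. The contrast is biased only if weekend and weekday sleep truly differ and weekend nights are lost unevenly by condition. At an assumed 15-minute difference and the assumed validity rates, the bias is about 1.0 to 1.6 min; it is zero if loss is unrelated to condition. The formula rests on no variance assumption, but the weekend difference and the loss rates are assumptions throughout. No conclusion about an inflated standard error should be drawn. The change is worth making because it is small and makes the article's claim true for incomplete weeks.

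**What to change.** 1. Prespecify a fixed effect for weekend night, defined from the recording date (for example Friday and Saturday nights versus the others), in the night-level model for SOL, WASO and the key secondary EEG outcomes. This requires first settling that nights are the unit of analysis, since the Statistical Analysis Plan section currently says both.
2. Report valid nights per condition split by weekday and weekend.
3. Reword the Methodological Consideration sentence so that weekend bias is handled by this term rather than by averaging alone.

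Reweighting each week mean to five-sevenths weekday and two-sevenths weekend is not a good substitute: it is undefined for a week with no valid weekend night or no valid weekday night. At independent weekend validity of 0.50, 0.5 × 0.5 = 25% of such weeks would have no valid weekend night.

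The cost is one model term and one degree of freedom. The recording date comes with the device data, so nothing new is collected. Data collection is still under way and the analysts are to work on masked condition labels, so the change can still be prespecified. The term does not correct the standard error for correlation between nights of the same week (the ratio stayed at 0.69 to 0.81 with a participant-by-week SD of 8 min and a weekend difference of 10 or 20 min); that is a separate matter.
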